### Procedures

The experimental procedures will be conducted at the Municipal Pool of Paião, in Figueira da Foz. The research team will consist of a principal investigator, an examiner, a data analyst, and two intervention administrators. The SPIRIT schedule of the study protocol is presented in Fig 1.

**Fig 1 pone.0320858.g001:**
[figure not shown]
Schedule of enrolment, interventions and assessments.

#### Feasibility study.

To assess the need for any adjustments in the experimental procedures and evaluate the feasibility of the clinical study methodology, a trial of the data collection protocol will be conducted with two to three individuals who meet the study’s eligibility criteria.

#### Sample selection and characterization.

Participant recruitment has begun in September 2024 and is expected to be completed in January 2025. Participants will be invited and recruited to the study through posters, which will include a brief explanation of the study’s aims and procedures. Interested individuals will complete a written selection and characterization questionnaire, and the principal investigator will provide detailed information about all procedures involved in the study.

#### Randomization and Blinding.

Participants who meet eligibility criteria will be given an alphanumeric code to maintain data confidentiality and anonymity. Participants will be randomly assigned to either ALG or AG, with a 1:1 allocation. Randomization will be performed by the principal investigator using a block randomization method generated by a computer program to ensure equal sample sizes in both groups. The block size will not be disclosed to maintain concealment. Participants will be informed of their group allocation (ALG or AG) via telephone contact. The principal investigator will not be actively involved in the intervention, data collection or data analysis. Randomization will only be known to the physiotherapists responsible for the intervention and the principal investigator. The examiner will evaluate participants before the intervention and after 8 weeks of intervention, ensuring blinding to group allocation, and participants will be asked not to disclose this information to the examiner. Each intervention will have a physiotherapist responsible for its execution, who will be instructed not to reveal participants’ group allocation to other research team members. Both data collector and data analyst will be unaware of the participants’ group distribution and will also be considered blinded. Only the principal investigator will have full knowledge of the entire research flow.

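### The investigator who informs candidates also runs the randomisation, the stated safeguard does not bind that person, and M0 is not placed before disclosure of the arm

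*Protocol article*

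**What the plan says.** All of this is in the protocol article.

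- **Contact with candidates** (Sample selection and characterization). "Participants will be invited and recruited to the study through posters". Interested people complete a selection questionnaire, and "the principal investigator will provide detailed information about all procedures involved in the study". Nobody is named as judging eligibility or enrolling.
- **Who randomises** (Randomization and Blinding). "Randomization will be performed by the principal investigator using a block randomization method generated by a computer program".
- **Who knows the result** (same section). "Randomization will only be known to the physiotherapists responsible for the intervention and the principal investigator".
- **Concealment measure** (same section). "The block size will not be disclosed to maintain concealment". From whom it is withheld is not said.
- **Separation of roles** (same section). "The principal investigator will not be actively involved in the intervention, data collection or data analysis".
- **Disclosure to participants** (same section). "Participants will be informed of their group allocation (ALG or AG) via telephone contact". No time is given. The sentence that has the examiner assess participants before the intervention and at 8 weeks, blinded, adds that "participants will be asked not to disclose this information to the examiner".
- **Timing of M0** (Data Collection). M0 comes after enrolment. Each session opens with the self-completed questionnaires and the VAS. No sentence relates M0 to randomisation.

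**The concern.** Concealment means that whoever can influence whether, or when, a candidate enters the trial cannot foresee the assignment that candidate would receive. Here the person who speaks to candidates and the person who runs the sequence are the same, and the one measure offered for concealment is aimed at other people. Foreknowledge would leave room for selective encouragement or timing. Some exclusions in the Participants section call for judgement, such as conditions that might prevent full participation or psychiatric disorders that might affect adherence. With 15 participants planned per group, a few such decisions could disturb the balance that randomisation is meant to give.

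The second strand is the baseline. All three primary outcomes (VAS, ODI, SF-36) are self-reported. A participant who already knows whether the extra land sessions are coming may answer M0 differently, and a blinded examiner cannot prevent that. The planned 2×3 within-between ANOVA compares change over time between groups, so it depends on M0 being comparable.

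**Working it through.** The point is about procedure, so most of the check sets statements side by side. The arithmetic only shows what the block-size safeguard can and cannot do.

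**1. The plan's own figure.** The Participants section gives an effect size of 1.079, α = 0.05, power 80% and 15 per group. A two-sample t-test (noncentral t, two-sided assumed because sidedness is not stated) needs 14.51 per group, rounded up to 15, or 30 in total. Power at 15 per group is 81.4%. The figure reproduces. It matters here only because it shows how small the trial is.

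**2. The investigator's roles.**

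| Task | Principal investigator's role as stated |
|---|---|
| Informing candidates | Yes |
| Judging eligibility, enrolling | Nobody named |
| Performing randomisation | Yes |
| Knowing allocations | Yes |
| Intervention, data collection, analysis | Not actively involved |

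The separation covers only the last row. It does not reach the stage at which concealment operates.

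**3. What an undisclosed block size achieves.** Suppose someone knows the block size b = 2m and all past assignments, with 1:1 permuted blocks. Block sizes here are assumptions, since the document rightly gives none.

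- Share of assignments known with certainty: 1/(m + 1).
- Share guessed correctly by always naming the arm with more places left: [m + (2^(2m)/C(2m, m) − 1)/2] / (2m).

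| Block size (assumed) | Known with certainty | Best guess correct |
|---|---|---|
| 2 | 1/2 = 50% | 1.5/2 = 75% |
| 4 | 1/3 = 33% | 2.833/4 = 71% |
| 6 | 1/4 = 25% | 4.1/6 = 68% |
| 8 | 1/5 = 20% | 5.329/8 = 67% |

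Exact enumeration of all sequences gives the same values. Withholding the block size therefore does useful work against an observer who sees past assignments. It does nothing against a person who holds a sequence generated in advance, for whom no guess is needed.

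**4. Order of M0 and disclosure.** The Randomization and Blinding section describes, in this order: eligible participants receive a code, they are randomised, they are telephoned, and the examiner assesses them before the intervention and at 8 weeks. The request to keep the arm from the examiner sits in that last sentence. If it applies to the pre-intervention visit, it serves a purpose only when the arm is already known. If it applies only to the 8-week visit, it says nothing about M0. Both readings fit the text.

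**5. How a baseline shift would travel.** The between-group contrast in change is (M1 − M0) in ALG minus (M1 − M0) in AG. If knowledge of the arm shifts mean M0 in AG by s relative to ALG, this contrast moves by s in absolute value. The document gives no basis for s or its sign. If AG participants, told of the smaller programme, reported more pain at M0, their apparent improvement would grow and the bias would run against the combined programme. The opposite shift would favour it.

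**The case against.** The case on the other side is substantial, and several stronger readings do not survive it.

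- **A reader might infer that the investigator recruits.** The text says that posters recruit and the investigator informs. What stands is narrower: no other team member is described as dealing with candidates at that stage.
- **A reader might infer that the next assignment is always known.** The text describes neither a list prepared beforehand nor anyone consulting one before an enrolment decision. Eligible participants could be assigned singly after eligibility is fixed, or in batches, and aquatic sessions in groups of 8–12 make batches plausible. Foreseeability therefore depends on the sequence being generated in advance. The file linking codes to identities, described under Ethics, is not an allocation list and does not show foreknowledge.
- **A reader might infer that participants know their arm at M0.** No sentence says so: the call is untimed and the request may concern only the 8-week visit. Figs 1 and 2, where the order would be expected, are not available here.
- **A reader might call the design unprotected.** That is too strong. The sequence is computer-generated, the block size is withheld, examiner and analyst are blinded, and the physiotherapists are told not to reveal allocation.
- **A reader might put a figure in millimetres on the bias.** Any baseline shift or correlation used for that would come from outside the document.

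It can also be said that an article leaves release procedures to the full protocol. That is fair for finer details such as block sizes and the mechanics of release. It does not answer the main point, because the article does state its concealment measure and who randomises, and the measure as stated does not bind that person.

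**Conclusion.** The concern holds in a limited form. The stated procedure gives candidate information, randomisation and knowledge of allocations to one person, relies on a measure that cannot conceal the sequence from that person, and omits enrolment from that person's separation. This is a weakness in what is written, not a missing detail. That the next assignment is actually foreseeable rests on one assumption, that the sequence is generated in advance.

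The M0 strand is weaker. The text leaves the order open and leans towards disclosure before M0, but does not establish it, and the figures may resolve it.

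Neither the size nor the direction of any resulting bias can be derived from the document, and nothing in it shows that bias occurred. The point merits a change because the trial is small, its primary outcomes are self-reported, and the remedy is cheap.

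**What to change.** For participants not yet allocated:

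- Let an automated randomisation tool, or a person who has no contact with candidates, generate and hold the sequence.
- Release each allocation only after consent, eligibility and the complete M0 assessment are recorded.
- Make the telephone call after that release, and state this order under Randomization and Blinding and under Data Collection, consistent with Figs 1 and 2.

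For participants already allocated, report who generated and held the sequence, whether it existed before enrolment decisions were made, and whether M0 was completed before or after the call. Recruitment was expected to finish in January 2025, so this may be the part that applies to most or all participants.

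The cost is a small set-up task and a fixed order for steps that already exist. No extra visit is needed. If M0 already precedes the call, that part needs only a sentence saying so.

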#### Data Collection.

After enrollment, participants will complete three evaluation phases: before the intervention (M0), after the intervention (M1), and 4 weeks after the end of the intervention (M2). Data collection started in November 2024 and is expected to be completed in April 2025. During data collection, participants will start each data collection session by filling out the questionnaires (Oswestry Disability Index, MOS Short Form Health Survey 36 Item, and Tampa Scale of Kinesiophobia-13) and the Visual Analog Scale for pain at rest, during movement, and at night, which will take approximately 30 minutes. Following this, the physiotherapist responsible for the assessment will measure weight and height, and then assess lumbar spine mobility using the Modified-Modified Schober Test, taking the best of three measurements. To standardize data collection, each participant will be asked to stand barefoot on a paper where the outline of their feet will be drawn to ensure consistent positioning across all measurements. This procedure will be repeated three times, with a 30-second break between repetitions. Participants will be instructed to place their feet at hip-width apart and their upper limbs relaxed along the body in the test starting position [68,69]. Fig 2 shows the study design with key moments of the intervention and data collection.

**Fig 2 pone.0320858.g002:**
[figure not shown]
Study design with key moments of the intervention and data collection.

### Outcome measures

#### Sample Selection and Characterization Questionnaire.

A questionnaire will be developed to select and characterize the study sample. It will collect personal data (age and sex), anthropometric data (height and weight), symptom duration, comorbidities, and professional status.

#### Primary outcomes

**Visual Analogue Scale (VAS).** The VAS is a unidimensional measure of pain intensity used to track its progression over time. This instrument consists of a 100-millimeter line, presented either vertically or horizontally, with an initial value of 0 indicating “No Pain" and an end value of 10 representing “Worst Pain." Participants are asked to mark a perpendicular line on the scale that corresponds to their level of pain. The scale is recorded on a single-use sheet of paper, and the value is obtained by measuring the distance from the origin (0) to the mark [70]. The VAS is a validated tool for assessing the intensity of CLBP, with moderate to strong construct validity (0.50–0.81), moderate to excellent test-retest reliability [Intraclass Correlation Coefficient (ICC) = 0.49–0.90], and a standard error of measurement (SEm) of 0.1% [71]. Additionally, the minimal clinically important difference (MCID) for this instrument is 20mm for CLBP [72].

**Oswestry Disability Index – version 2.0 (ODI).** The ODI is a tool used to measure and assess the disability caused by low back pain. It consists of 10 questions, each rated on a Likert scale from 0 to 5, where 0 represents no dysfunction and 5 represents the highest level of dysfunction. The final score is expressed as a percentage, indicating the level of disability experienced by the individual with low back pain: 0%–20% (minimal disability); 21%–40% (moderate disability); 41%–60% (severe disability); 61%–80% (very severe disability); 81%–100% (exaggerated symptoms) [73,74]. This instrument has been translated and validated for the Portuguese population, showing a good correlation with the MOS Short Form Health Survey 36 (r=−0.59 to –0.75) and excellent internal consistency (Cronbach’s α = 0.95) and reproducibility (ICC = 0.90) [75,76]. The MCID for this questionnaire was established at 10% [72,77].

**MOS Short Form Health Survey 36 Item v2 (SF-36 v2).** The SF-36 v2 questionnaire is an assessment tool primarily designed to measure and evaluate the health status and quality of life of populations and individuals, whether they have health conditions or not. It consists of 36 items, rated on a scale from 1 to 5 (Likert scale). The questionnaire is divided into 8 dimensions (physical functioning, physical role limitations, bodily pain, general health perceptions, energy/vitality, social functioning, emotional role limitations and mental health), which can be grouped into two components (physical health and mental health). Scores for each dimension are presented on a positively oriented scale from 0 (worst health state) to 100 (best health state) [78]. The instrument was previously validated and translated for the Portuguese population, demonstrating good content validity (*r*>0.401) and moderate to excellent levels of internal consistency (Cronbach’s α = 0.60–0.87) and test-retest reliability (ICC = 0.45-0.84) across its various domains [79,80]. For this instrument, the MCID has been established at 6 for mental health and 14 for physical health [81].

#### Secondary outcomes

**Tampa Scale of Kinesiophobia-13 (TSK-13).** The TSK-13 is a simple tool designed to quantify fear of movement or (re)injury. The questionnaire consists of 13 items, rated on a 4-point Likert scale (strongly disagree, disagree, agree, and strongly agree), with a final score ranging from 13 to 52 points [82]. The final classification of fear of movement can be categorized as subclinical (13–22), mild (23–32), moderate (33–42), and severe (43–52) [83]. The questionnaire has been translated for the Portuguese population, with construct validity established through its correlation with the VAS for pain intensity (r=0.691) and confidence in movement (r=−0.772). The instrument shows excellent reliability (ICC = 0.94–0.98) and internal consistency (Cronbach’s α = 0.82) [84]. The MCID for this questionnaire has been established at 5.5 points [85].

**Modified-Modified Schober Test (MMST).** The MMST is a test originally designed to determine whether there is a reduction in lumbar spine range of motion due to various health conditions such as CLBP. It has subsequently been used to measure the effects of therapeutic interventions on lumbar mobility [86]. To perform this test, the participant should be in an upright position so that the examiner can mark both Posterior Superior Iliac Spines (PSIS) using a skin marker, then draw a horizontal line between them and mark a point at the intersection of this line with the spine (center of both marks). Next, the examiner should mark a second point 15 cm above the first. The participant is then instructed to bend the trunk as if trying to “touch their toes”, and the examiner should measure the distance between the upper and lower lines again. An increase of less than 5 cm in the measured distance indicates a decrease in lumbar spine range of motion [87]. The MMST is a validated test for individuals with CLBP, showing a moderate correlation (r=0.67) with the gold standard metric (X-ray) and excellent reliability, specifically in interclass correlations (r=0.91) and intraclass correlations (r=0.95) [88]. For this test, the minimal detectable difference is 1 cm [89].

**Anthropometry.** Body mass will be assessed using a portable scale (Inbody 270, USA) with an accuracy of 0.1kg, while participants will be asked to wear minimal clothes. Height will be measured using a portable stadiometer (SECA Bodymeter 208, Germany), with an accuracy of 1 millimeter, following standardized procedures [90]. Body Mass Index (BMI) will be calculated using the formula: $\text{BMI}=({\text{weight/height}}^{2})$ [91]. Skeletal muscle mass (kg), fat mass (kg), bone mineral mass (%), and body fat (%) will be assessed using the tetrapolar bioimpedance (Inbody 270, USA). The impedance measurements will be performed according to the literature and manufactory recommendations [92].

### Adverse events

During the procedures, participants may experience some adverse events and should be aware of the potential risks during both the assessment phase and the intervention. To address this, a cardiovascular risk assessment will be conducted to contraindicate the performance of physical exercise/activity according to the American College of Sports Medicine flowchart, and the PAR-Q questionnaire will be administered. Participants classified as high risk will be excluded from the study to minimize the risk associated with physical exercise. For the remaining risk categories, the risk of a cardiovascular event is null or reduced [13]. Participants will be instructed to regularly check their skin and contact the principal investigator if they experience a rash, redness, itching, or any other sign of an allergic reaction, although such adverse reactions are rare [37]. Thus, the physiotherapist will record any adverse events that may occur by asking participants if they have experienced any health issues (injuries, pain, etc.) since the previous session. All adverse events will be reviewed by the research team and appropriately referred for clinical treatment or rest.

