### Intervention

The intervention will take place over 8 weeks at the Municipal Pool of Paião, located in Figueira da Foz, Portugal. The AG will conduct the aquatic exercise program, while the ALG will carry out both aquatic and land-based exercise programs. The intervention will begin after a one-week washout period, during which participants will cease any additional physical exercise, which they will maintain throughout the intervention weeks.

To monitor the intensity of the interventions, Borg CR-10 scale will be used. This is a tool to rate dyspnea and/or perceived exertion (RPE) experienced by an individual. The scale consists of a numerical list with 10 points (0–10), an adaptation of the original scale (6–20), that assesses and monitors the intensity/severity of shortness of breath/fatigue. Its use requires explaining that “0" means not experiencing dyspnea/fatigue at the moment and that “10" means the worst dyspnea/fatigue they have ever experienced or the worst imaginable dyspnea/fatigue [57,58]. This instrument will not be used during the assessment moments before and after the exercise programs but only to monitor the intensity during the sessions of both aquatic and land-based exercise programs. This scale is validated for monitoring dyspnea and fatigue, showing an excellent correlation with heart rate (r=0.92) and VO2 (*r*=0.92–0.93) and moderate reliability (ICC=0.50–0.66) [59].

Participants will be encouraged to maintain their daily activities as usual outside of the study. The participants may not participate in any other exercise programs.

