#### Aquatic-exercise program.

This intervention will consist of an aquatic-exercise program (Table 1), administered by a physiotherapist. It will include 16 sessions, twice a week, over 8 weeks at a water temperature between 32–34 ∘ C. Each session will be conducted in groups of 8–12 patients and will last about 45 minutes. The aquatic exercise sessions will include a warm-up phase (5 minutes): walking forwards, sideways, and backwards; a training phase (35 minutes): active range of motion exercises (10 minutes) for the spine, upper and lower limbs; aerobic exercises (5 minutes) with jumps and static running at various speeds; muscle strengthening (10–15 minutes), (8–12 repetitions), 1–2 sets, 8–10 exercises including hip flexion, extension, adduction, and abduction, knee flexion and extension, knee cycling, shoulder flexion, extension, and abduction, elbow flexion, extension, and pronation-supination, squatting, and stretching exercises (5–10 minutes) for the neck, trunk, and limbs; and a relaxation/cool-down phase (5 minutes): including lying supine and low-impact exercises such as slow walking, squatting, and standing [20,37,38,41,42]. For participants who cannot complete any exercise due to difficulty or discomfort, a modified version of each exercise will be offered. The load progression will be managed using auxiliary equipment, including flotation devices, plates, balls, pull-buoys, and dumbbells, according to each participant’s RPE on the Borg CR-10 scale.

**Table 1 pone.0320858.t001:** Aquatic-exercise program.

Type	Frequency and duration	Intensity	
		Week 1–4	Week 5–8
Aquatic exercise: aerobic, resistance, and flexibility training performed in water.	2 times per week. Session duration: 40–45 min (warm-up phase: 5 min, training phase: 30–35 min; and relaxation/cool-down phase: 5 min).	Warm-up phase:	Warm-up phase:
		Low-intensity aerobic exercise: walking forwards, sideways, and backwards. RPE: 3–4 (Borg CR-10 Scale).	Low-intensity aerobic exercise: walking forwards, sideways, and backwards. RPE: 3–4 (Borg CR-10 Scale).
		Training phase:	Training phase:
		Active range of motion exercises: spine, upper and lower limbs. RPE: 3–4 (Borg CR-10 Scale).	Active range of motion exercises: spine, upper and lower limbs. RPE: 3–4 (Borg CR-10 Scale).

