#### Land-exercise program.

This program will include specific land-based exercises (Table 2, guided by a physiotherapist. This intervention will include 8 sessions in 8 weeks, once a week, on a different day from the aquatic exercise program. Each session will last between 25 to 35 minutes and will be divided into two components: core stability exercises and stretching of the trunk and lower limbs [60]. Core stability exercises (15–20 minutes): these will consist of isometric exercises which contraction was maintained for 7–8 seconds, 8–12 repetitions, 1 set, with brief rest intervals of 3 seconds between repetitions and 30 seconds to 1 minute between exercises [60,61]. Exercises will include abdominal hollowing, side bridge (both sides), supine extension bridge, lower limb extension from prone (both sides), and alternate arm and leg raise from quadruped. Intensity will increase gradually by reducing rest time between exercises and increasing repetitions, based on participants’ performance. Participants will be instructed to contract and hold their abdominal muscles while maintaining normal breathing patterns [62]. Stretching exercises (10–15 minutes): participants will perform muscle stretching exercises, holding the maximum stretch for 30 seconds to 1 minute, and returning to the original position, followed by 5–10 seconds of rest. Each exercise will be repeated two to three times [63]. Stretches will target the hamstrings, iliopsoas, piriformis, and tensor fasciae latae. Participants will be instructed to minimize tension in other body muscles and maintain their usual breathing pattern during stretching [64–67].

**Table 2 pone.0320858.t002:** Land-exercise program

Type	Frequency and duration	Intensity	
		Week 1–4	Week 5–8
**Core stability exercises:** abdominal hollowing, side bridge (both sides), supine extension bridge, lower limb extension from prone (both sides), and alternate arm and leg raise from quadruped, performed in dry land.	1 time per week. Session duration: 25–35 min	**Isometric strength exercises:** contraction held for 7–8s, 8–10 reps, 1 set.	**Isometric strength exercises:** Contraction held for 9–10s, 10–12 reps, 1 set.
	(Core stability exercises: 15–20 min, and stretching exercises: 10–15 min).	Rest between reps: 3s	Rest between reps: 3s
		Rest between exercises: 1min.	Rest between exercises: 30s.
		RPE: 5–6 (Borg CR-10 Scale)	RPE: 6–7 (Borg CR-10 Scale)

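### Adverse events are actively sought only at attended exercise sessions, so injuries or pain flares after a participant's last session, including the four weeks to M2, are not asked about

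*Protocol article*

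**What the plan says.** The Adverse events section of the protocol article names who asks, how, and over what recall window: the physiotherapist, by "asking participants if they have experienced any health issues (injuries, pain, etc.) since the previous session". It gives one further route, which does not depend on sessions: participants are to check their skin and "contact the principal investigator if they experience a rash, redness, itching, or any other sign of an allergic reaction". The section also says that risks can arise in the assessments as well as in the exercise programme.

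The two arms have different session schedules. The Intervention section states: "The AG will conduct the aquatic exercise program, while the ALG will carry out both aquatic and land-based exercise programs". For the aquatic programme: "It will include 16 sessions, twice a week, over 8 weeks". For the land programme: "This intervention will include 8 sessions in 8 weeks, once a week, on a different day from the aquatic exercise program".

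The Data Collection section places the last assessment "4 weeks after the end of the intervention (M2". It lists what is done at each assessment: three questionnaires, the pain scales, weight and height, and the Schober test. No adverse-event question is among them. The Participant adherence section provides for contact after two consecutive missed sessions, and the stated purpose is resumption of the sessions.

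**The concern.** Because the question is put at a session and looks back to the one before, it stops when attendance stops. A participant who leaves because of an injury or a flare is the person whose event most needs recording, and is not asked about it. The protocol expects losses: it plans a 15% allowance per group, and its Discussion lists problems with the programmes among the known causes of dropout.

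The same limit applies after week 8. Training cessation is a stated objective, yet no one is asked about events in that period. M2 will show pain and disability scores, but a score does not record that an injury happened, when, or why.

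A lesser matter is that the arm with more sessions is asked more often, by physiotherapists who know the allocation. This would complicate any comparison of event counts between arms.

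**Working it through.** **Inputs** (protocol article): aquatic sessions twice a week for 8 weeks, both arms; land sessions once a week for 8 weeks on other days, ALG only; M2 at 4 weeks after the intervention; 80% attendance threshold (Participant adherence).

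**1. The plan's own session counts.** Aquatic: 2 × 8 = 16. Land: 1 × 8 = 8. Both stated figures reproduce.

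**2. Time without active enquiry.** From the first session to M2 is 8 + 4 = 12 weeks. Sessions cover 8 of these. The remaining 4/12 = 33% have no enquiry in either arm. For a participant who stops early, the uncovered part is longer: someone whose last session is at the end of week 4 is not asked about 8 of 12 weeks (67%).

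**3. Other contacts that might close the gap.**

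| Contact | Stated content | Covers injury or pain flare? |
|---|---|---|
| Exercise session | Health issues since the previous session | Yes, if attended |
| Self-report to principal investigator | Skin or allergic signs | No |
| Contact after two missed sessions | Resuming sessions | Not stated |
| M1 and M2 assessments | Questionnaires, pain scales, weight and height, Schober test | Not stated |

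Only the first row asks about injury or pain as an event. A participant who misses sessions and returns is asked about the gap. One who does not return is not.

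**4. Prompts by arm.** AG: 16. ALG: 16 + 8 = 24, since land sessions fall on separate days. Ratio 24/16 = 1.5. At the 80% threshold: 0.8 × 24 = 19.2, so at least 20; 0.8 × 16 = 12.8, so at least 13. Average recall is 7/2 = 3.5 days in AG and 7/3 = 2.3 days in ALG.

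**5. What unequal prompting could do.** The documents give no reporting rate, so the two extremes are assumptions.
- *Complete recall.* Each event is reported at the next session. Regular attenders are covered for the same eight weeks in both arms, so the ratio of counts due to prompting is 1.0.
- *Each prompt independently yields a report with the same probability q, however long the interval.* Expected reports are 16q and 24q, ratio 1.5. The chance of at least one report, 1 − (1 − q)^16 in AG and 1 − (1 − q)^24 in ALG, is 14.9% v 21.4% at q = 0.01, 27.6% v 38.4% at q = 0.02, and 56.0% v 70.8% at q = 0.05.

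The second case is an upper illustration: it ties events to questions rather than to time. The documents do not say where between 1.0 and 1.5 the truth lies.

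**6. Real exposure also differs.** At about 45 minutes per session, aquatic exercise totals 16 × 45 = 720 minutes. Land sessions of 25 to 35 minutes add 8 × 25 = 200 to 8 × 35 = 280 minutes, or 28% to 39% more in ALG. Real extra events are therefore plausible, and session-collected counts cannot separate them from extra asking.

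**The case against.** The strongest objection is that a journal article condenses the full protocol, which may contain a safety question at M1, M2 or withdrawal. The article does not say that the session question is the only method, and it says that all adverse events will be reviewed. This stands in part: the point concerns what the article fixes, and a fuller document could close the gap. But the article is not silent. It specifies the asker and the recall window, and it lists assessment procedures without an adverse-event question. That is a stated method with a gap.

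Three stronger readings are tempting, and the documents do not support them.
- A reader might infer that nothing is captured outside sessions. The skin and allergy route is open at any time.
- A reader might infer that ALG counts will be inflated. For attenders the question covers the same eight weeks in both arms. Only the number of prompts and the recall length differ, by about 3.5 − 2.3 = 1.2 days on average, and no figure shows how much is forgotten in that time.
- A reader might infer that a planned safety comparison is biased. Adverse events are neither a primary nor a secondary outcome, and the Statistical analysis section states no safety test between arms. The caution applies to any tabulation by arm.

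It is also fair that a lasting rise in pain or disability would appear in the M2 outcome data. It would not be recorded as an event, and resolved or non-back injuries could leave no trace there.

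**Conclusion.** The point holds as a gap in safety capture, of minor severity. As written, injuries and pain flares are not asked about after the last attended session, nor in the 4 of 12 weeks up to M2. This rests on reading the article's procedures as the ones that will be followed.

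The 24 v 16 difference in scheduled prompts is exact but secondary. Prompting alone could shift session-collected counts by a factor somewhere between 1.0 and 1.5 under the assumptions above, alongside a real difference in exposure. It is a reason not to compare those counts directly; it does not show bias in either direction. The efficacy analyses are not affected.

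**What to change.** 1. Keep the session question unchanged.
2. Add one scripted adverse-event question, identical in both arms, for every randomised participant at M1 and at M2, whatever their attendance. Make it self-completed with the other questionnaires and handed in closed, so that the examiner stays blinded.
3. Put the same question in the contact already planned after two consecutive missed sessions.
4. Base any between-arm safety summary on the M1/M2 question in all randomised participants, and state that the 80% attendance exclusion does not apply to it. Report session-collected events separately, with the number of prompts per arm. A summary of participants with at least one event from any source would still carry the unequal prompting.
5. The Data Collection section expects completion in April 2025. If the visits are already over, report the enquiry schedule and its gaps beside the event counts.

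The cost is about one minute per visit or contact, with no extra visit or staff. The drawback is longer recall: up to eight weeks at M1 and four at M2, so minor events will be under-reported, though over the same recall period in both arms. A participant who neither attends M1 or M2 nor answers the contact would still be missed, and the number of such participants should be given per arm.
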